## 3.5 Inclusion/exclusion criteria

Exclusion criteria:

- Age 17 or less at the study start date (8^th^ December 2020)
- Deceased prior to the study start date (8^th^ December 2020)
- Those living in an elderly care home (household with more than 10 people and an average age of over 65 as proxy)

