## 5.2 Outcomes of interest

The primary outcome will be a composite outcome of time to COVID-19 hospitalisation or death. COVID-19 hospitalisation will be defined as a RT-PCR confirmed positive test for SARS-CoV-2 in the 28 days prior to admission, or with ICD-10 code for COVID-19 (in any diagnostic position). COVID-19 deaths will be defined as COVID-19 as the underlying ICD-10 cause of death recorded on the death certificate, or death from any cause within 28 days of a positive RT-PCR test for SARS-CoV-2 infection.

Secondary outcomes will be the single outcomes of: a) COVID-19 hospitalisation (as defined above), and b) COVID-19 deaths.

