### 5.5.2 Matched analysis

To create control groups for our primary analysis, we will emulate a ‘target trial’. We will do this by conducting 1:1 risk-set matching to identify individuals who had not yet become exposed (i.e. remained unvaccinated) on the date an exposed person received their vaccine dose. We will do this using a time-varying propensity score matching algorithm, by fitting separate propensity score models by month.

Due to the strong confounding effect of living in an elderly care home (arising from the targeted vaccination of these residents and their high risks of COVID-19 harms) and the lack of available controls, we will exclude people whose household had more than 10 people with an average age of 65 years and over. This will be used as a proxy for those living in an elderly care home.

We will incorporate the following characteristics into the time-varying propensity score model: sex, age (grouped in 5 year bands), SES, number of risk factors (grouped), number of previous SARS-CoV-2 tests pre-vaccination era (grouped), geography (local authority level), urban-rural settlement, average household age, number of people in household (grouped), smoker indicator, BMI (grouped), presence in hospital status (hospitalised for any reason 4 weeks prior to monthly time-period) and previous positive test indicator (tested positive previous to monthly time-period). Individuals will then be matched using exact matching based on the propensity score in 1% bands, local authority, and age (exact age in years, truncated up to 100 years). The adequacy of the matching will be assessed by checking for imbalance of the individual covariates and the individual risk groups across exposure groups.

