We expect that any effects before 14 days for first dose vaccination will reflect programmatic effects (e.g. being instructed not to attend vaccination if symptomatic and reinforcement of behavioural advice to reduce COVID-19 related risks). Follow up will therefore start from day 14 after the date of first dose vaccination (and day 7 after second dose) for both the exposed and control person. It will end for both the exposed and control person on the first of: experiencing the outcome of interest, death (from any cause) or end of follow up period. Unvaccinated controls who become vaccinated will be eligible to become considered as exposed, after follow up is censored for the exposed-unexposed pair at the date of vaccination of the control. Follow-up of the exposure period will also be censored for both the recipient and the control if the partially vaccinated recipient participant received a second dose. Analyses will be stratified by vaccine type.

For the matched cohort analysis, we will draw Kaplan Meier curves to inspect cumulative incidence. We will then fit Poisson regression models to estimate rate ratios (RRs) with 95% confidence intervals (95% CIs) for the association between exposure group and risk of the outcomes, at weekly time periods from exposure to event (Section 4.2).

We will fit a model including a spline with person-time defined in days, to explore the timing of any waning of vaccine effectiveness. The splines will be fit using thin plate regression splines (the R package ‘mgcv’ default settings) with weekly knots from days 14 to the maximum week. The difference between the smooths in the exposure groups will be calculated using methods by Simpson, [7] to obtain smoothed estimated RRs between the exposure groups at daily follow-up periods.

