**Second dose:**

| Second dose vaccinated | Matched |
| --- | --- |
| 2,582,105 | 1,358,286 (52.6%) |

Population characteristics for vaccine controls and vaccine recipients by vaccine type in matched cohort analysis (excluding care home residents)

Code: 03c_matching_ps_summary.R (lines 102-169)

| **Characteristic** | **Level** | **Both vaccines** | | **BNT162b2** | | **ChAdOx1** | |
| --- | --- | --- | --- | --- | --- | --- | --- |
|  |  | **Unvaccinated** | **Vaccinated** | **Unvaccinated** | **Vaccinated** | **Unvaccinated** | **Vaccinated** |
| Total | | 2573874 | 2573874 | 833719 | 833719 | 1740155 | 1740155 |
| COVID-19 hospitalisation or death | All events, N (Rate per 1000*) | 2173 (8.9) | 1005 (4.1) | 840 (8.3) | 369 (3.7) | 1333 (9.2) | 636 (4.4) |
|  | Events 14 days+, N (Rate per 1000*) | 1029 (4.4) | 541 (2.3) | 488 (5) | 238 (2.4) | 541 (4) | 303 (2.2 |
| Sex | Female | 1418102 (55.1%) | 1403332 (54.5%) | 507290 (60.8%) | 508427 (61.0%) | 910812 (52.3%) | 894905 (51.4%) |
|  | Male | 1155772 (44.9%) | 1170542 (45.5%) | 326429 (39.2%) | 325292 (39.0%) | 829343 (47.7%) | 845250 (48.6%) |
| Age (years) | Mean (SD) | 57.9 (15.7) | 57.9 (15.7) | 56.1 (16.4) | 56.1 (16.4) | 58.8 (15.2) | 58.8 (15.2) |
|  | Median (IQR) | 58 (20) | 58 (20)` | 60 (23) | 60 (23) | 58 (19) | 58 (19) |
| Age group (years) | 18-64 | 1680152 (65.3%) | 1680152 (65.3%) | 491221 (58.9%) | 491221 (58.9%) | 1188931 (68.3%) | 1188931 (68.3%) |
|  | 65-79 | 691534 (26.9%) | 691534 (26.9%) | 319944 (38.4%) | 319944 (38.4%) | 371590 (21.4%) | 371590 (21.4%) |
|  | 80+ | 202188 (7.9%) | 202188 (7.9%) | 22554 (2.7%) | 22554 (2.7%) | 179634 (10.3%) | 179634 (10.3%) |
| Deprivation status † | 1 - High | 478638 (18.6%) | 468522 (18.2%) | 159802 (19.2%) | 152724 (18.3%) | 318836 (18.3%) | 315798 (18.1%) |
|  | 2 | 507601 (19.7%) | 503069 (19.5%) | 164176 (19.7%) | 163837 (19.7%) | 343425 (19.7%) | 339232 (19.5%) |
|  | 3 | 529350 (20.6%) | 525676 (20.4%) | 170884 (20.5%) | 165730 (19.9%) | 358466 (20.6%) | 359946 (20.7%) |
|  | 4 | 537544 (20.9%) | 539520 (21.0%) | 174078 (20.9%) | 178153 (21.4%) | 363466 (20.9%) | 361367 (20.8%) |
|  | 5 - Low | 508818 (19.8%) | 525164 (20.4%) | 160895 (19.3%) | 169391 (20.3%) | 347923 (20.0%) | 355773 (20.4%) |
|  | Unknown | 11923 (0.5%) | 11923 (0.5%) | 3884 (0.5%) | 3884 (0.5%) | 8039 (0.5%) | 8039 (0.5%) |

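### No match-date eligibility rule on infection or outcome status, so infections detected before matching can still count as control events on days 14–28

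*SAP*

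**What the plan says.** **Who can be a control.** Section 5.5.2 uses risk-set matching to "identify individuals who had not yet become exposed (i.e. remained unvaccinated) on the date an exposed person received their vaccine dose". That is the only status required on the match date. The exclusions in section 3.5 are age 17 or less, the elderly care home proxy, and "Deceased prior to the study start date". None concerns recent infection, a current hospital stay, or having already had the outcome.

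**How infection and hospital status are used.** Both are terms in monthly propensity-score models: "previous positive test indicator (tested positive previous to monthly time-period" and "presence in hospital status (hospitalised for any reason 4 weeks prior to monthly time-period". Pairs are then "matched using exact matching based on the propensity score in 1% bands, local authority, and age", so neither variable is matched exactly.

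**The outcome.** Section 5.2 counts an admission with an "RT-PCR confirmed positive test for SARS-CoV-2 in the 28 days prior to admission", or with a COVID-19 ICD-10 code in any position. It counts a death within 28 days of a positive test, or with COVID-19 as the underlying cause.

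**The safeguard.** Section 5.5.2 expects effects before day 14 to be programmatic, naming the instruction not to attend with symptoms and the reinforcement of behavioural advice. It concludes: "Follow up will therefore start from day 14 after the date of first dose vaccination". A day-21 start (5.5.6) and a negative-control period (5.5.7) are listed only as things to be considered.

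**The concern.** A target-trial emulation should apply the same eligibility test to both groups at time zero. Here the vaccination appointment screens recipients for current illness, and nothing screens controls. The plan recognises the asymmetry and relies on a 14-day gap to remove it, but its outcome definition reaches back 28 days, so the gap covers only half of the look-back.

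The residue falls in the first two weeks of analysed follow-up, the baseline against which any later loss of effectiveness is judged. If infected recipients largely defer, early RRs look too favourable and then rise without any change in true protection. The weekly RRs, the spline and the second waning criterion in section 5.5.2 (whether the RR point estimate meets 0.5) are all open to this.

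**Working it through.** **1. Reproduce the template counts.** Inputs are from the matched-cohort characteristics table in section 5.6.2, unvaccinated against vaccinated ("All events, N (Rate per 1000*) | 2173 (8.9) | 1005 (4.1").

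- All events: 840 + 1333 = 2173 control; 369 + 636 = 1005 vaccinated.
- From day 14: 488 + 541 = 1029 control; 238 + 303 = 541 vaccinated.

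The vaccine-specific counts add to the totals.

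**2. Days 0–13 by subtraction.** With 1:1 pairs and near-equal person-time, RR ≈ vaccinated events / control events.

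| | Days 0–13 | Day 14+ |
|---|---|---|
| Both | (1005 − 541)/(2173 − 1029) = 464/1144 = 0.41 (95% CI 0.36–0.45) | 541/1029 = 0.53 (0.47–0.58) |
| BNT162b2 | 131/352 = 0.37 | 238/488 = 0.49 |
| ChAdOx1 | 333/792 = 0.42 | 303/541 = 0.56 |

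The apparent effect is stronger in the window the plan attributes to programmatic causes than in the window attributed to the vaccine.

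**3. How far a pre-match test can reach.** Put the positive test x days before matching and the event on day t after it. The test route requires t + x ≤ 28. With t ≥ 14, x must lie between 0 and 14. With x ≥ 0, t cannot exceed 28. The exposed stretch is therefore days 14–28.

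**4. What the month-start indicator can see.** For a match on day k of a 30-day month, min(k − 1, 14)/14 of the 14-day look-back lies inside the current month. Averaged over k = 1 to 30 this is (7.5 + 15)/30 = 0.75. So about 75% of the relevant look-back is invisible to the indicator. The other 25% is visible but leads to no exclusion.

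**5. Possible size, under assumptions.** The document gives no distribution of the lag from test to event. Assume a lognormal lag with median 3 to 14 days, truncated at 28, steady incidence, and a constant true RR of 0.526. Let s be the share of control events arising from pre-match tests, and d the frequency of such events in recipients relative to controls. Then RR observed = (1 − s) × 0.526 + s × d.

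- s is about 1% to 27% on days 14–20, 0.2% to 6% on days 21–27, and 0 after day 28.
- Complete deferral (d = 0): day 14–20 RR between 0.520 and 0.383.
- Partial deferral (d = 0.41, the days 0–13 ratio): 0.525 to 0.495.
- No deferral (d = 1): 0.532 to 0.655, the opposite direction.

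**6. Sensitivity of the 0.5 criterion.** For BNT162b2, 238/(488 − c) exceeds 0.5 once c > 12: 238/476 = 0.500 and 238/475 = 0.501. Thirteen events are 13/488 = 2.7% of control events. If v recipient events are removed too, the condition becomes c > 12 + 2v.

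**7. Effect on the quadratic test.** I fitted a Poisson quadratic over days 14–76 to expected counts from the model in step 5, under d = 0 and d = 0.41 and several assumed rates of loss of person-time. The vaccinated-minus-control quadratic term was negative in every run. When the excess was instead added to a flat control rate, the exposed group's own quadratic term was zero.

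**The case against.** The plan is not blind to the problem. It names symptomatic deferral, starts both pair members at day 14, and lists a day-21 start and negative-control periods. The day-14 start does discard the worst-affected stretch: 1144 of the 2173 template control events (53%) fall before it. By the test route the residue ends by day 28, so it cannot alone explain a later rise in the RR. All of this stands. It narrows the point but does not close the gap between a 14-day lead-in and a 28-day outcome window, and the listed checks are optional.

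Four stronger readings are tempting and should not be drawn.

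- *That the artefact would pass the plan's hypothesis test for waning.* An RR that starts low, rises and flattens is concave; step 7 shows it does not give a positive quadratic coefficient.
- *That the month-start reading is the root cause.* Both variables are propensity terms only, so reading them on the match date would still leave these people eligible. The missing eligibility rule is the main fault; the stale reading makes it worse.
- *That people in hospital at matching are a large source of events.* Their admission predates follow-up, so they contribute mainly through later death or readmission. The ICD-10 route does, however, have no test-date limit.
- *That the days 0–13 excess measures the bias after day 14.* The plan also names behaviour change, which the counts cannot separate from deferral. No count for days 14–27 is given.

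The counts are also template figures: the same section gives 1,650,185 matched first-dose recipients but 2,573,874 pairs in the table. They illustrate the issue; they are not a result.

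**Conclusion.** The point holds as a limited design gap. Section 5.5.2 applies no match-date rule on infection or outcome status, and the day-14 start does not fully remove the resulting asymmetry, because tests 0–14 days before matching can yield events on days 14–28.

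The direction depends on deferral. Early RRs are biased down only if recently infected people are rarer among recipients than the true RR implies. The plan's own account of the instruction to stay away makes that plausible, but nothing in the document establishes its extent. The size is not identifiable; the step 5 range rests entirely on an assumed lag and deferral. The practical stake is the weekly RRs, the opening of the spline and the 0.5 threshold. On the template counts, a net loss of 13 control events would move BNT162b2 across that threshold. The quadratic test is not pushed towards a false finding of waning.

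**What to change.** In section 5.5.2:

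- On the match date, require both members of each pair to be free of the outcome, not in hospital, and without a positive RT-PCR in the previous 28 days.
- Read the previous-positive-test and hospital-presence covariates on that same date.
- Report the days 0–13 RR, overall and by vaccine, as a check on selection.

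In section 5.5.6, replace the optional day-21 start with a firm sensitivity analysis starting after day 28. A day-21 start still lies inside the 28-day window.

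Do not re-apply the positive-test exclusion at day 14. That would select on infections arising after vaccination and add post-baseline selection.

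The cost is SAP wording and a filter on test and admission dates that sections 3.4 and 4.1 already list as data sources. Expect a small loss of pairs, and less early follow-up in the sensitivity analysis.

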# 3. Study Design

## 3.1 Study design

The primary study design is an open prospective cohort study with risk-set matching to emulate a ‘target trial’ comparing outcomes amongst first dose vaccinated (partially vaccinated) to people who have not yet been vaccinated [1-3]. To maximise statistical power, we will conduct secondary analyses using the entire study population.

The time period for the study will begin on the first date of vaccine administration in each UK nation, 8^th^ December 2020, and will end on the 30^th^ April 2021.

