## 3.3 Population

Individuals registered in General Practices (GPs) across the UK (~5.3 million for England, approx. 1.4 million for Northern Ireland, ~ 5.4 million for Scotland and ~3.1million for Wales).

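### Follow-up has no exit for people who deregister or move out of the nation, and controls need not be current residents, so the weekly rate ratios can drift with time since dose by an unknown amount and in an unknown net direction

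*SAP*

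**What the plan says.** SAP 3.1 describes an "open prospective cohort study with risk-set matching". The source population in 3.3 is "Individuals registered in General Practices (GPs) across the UK". The exclusions in 3.5 are age, the care-home proxy and "Deceased prior to the study start date"; none removes a person who has left but is still on a list. Under 5.5.2, eligible controls are those who "had not yet become exposed (i.e. remained unvaccinated) on the date an exposed person received their vaccine dose".

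Section 5.5.2 also fixes when follow-up stops. For both members it ends "on the first of: experiencing the outcome of interest, death (from any cause) or end of follow up period". Two further rules apply to the pair. A control who is vaccinated may re-enter as exposed "after follow up is censored for the exposed-unexposed pair at the date of vaccination of the control", and follow-up is "censored for both the recipient and the control if the partially vaccinated recipient participant received a second dose".

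The cohort analysis in 5.5.3 uses a time-at-risk offset without saying when a person's time at risk ends. Deregistration, out-migration and loss to follow-up are not mentioned anywhere in the SAP.

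**The concern.** A recipient is known to have been present on the match date, because a vaccination was recorded. A control is known only to have no vaccination record. Someone who has left the nation but remains on a GP list meets that test, cannot be vaccinated or admitted in the linked sources, and contributes event-free time. Present controls drop out as they are vaccinated and absent ones do not, so the absent share grows along the axis on which waning is judged.

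The omission also covers recipients who leave after their first dose. They too add event-free time, and a second dose never censors them.

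Both waning assessments in 5.5.2 depend on how outcome rates move over time since dose: one tests curvature, the other compares the RR point estimate with 0.5. An artefact that varies with time since dose could therefore change the answer to the primary question.

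**Working it through.** **Plan figures.** The SAP gives no count of leavers or inactive registrants, so there is no figure of its own to reproduce on this point. The filled-in matched table in 5.6.2 is at least consistent on the RR. From day 14, events give 541/1029 = 0.526 and rates give 2.3/4.4 = 0.523. Over all days, 1005/2173 = 0.462 and 4.1/8.9 = 0.461.

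**Absent controls.** Let g be the share of controls absent at matching (assumed, 1-5%), and S(t) the share of present controls still unvaccinated at day t. Then

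- g_t = g / (g + (1 - g) S(t))
- observed RR(t) = true RR / (1 - g_t)

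Take S(t) = exp(-t/m) and a constant true RR of 0.45, both assumptions.

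**Choice of m.** The table implies 2,173 / 8.9 x 1000 = about 244,157 control person-years. Over 2,573,874 pairs that is 34.6 days each. This counts every cause of pair loss, including the recipient's second dose and the 30 April 2021 cut-off, which remove pairs with absent controls just as readily as other pairs. It is therefore a fast extreme for control vaccination.

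It is also a soft figure. The first-dose match count in 5.6.2 is 1,650,185, and the same person-time over that number gives about 54 days. The printed day-14+ rate implies 1,029 / 4.4 x 1000 = about 233,864 person-years, only about 1.5 days per person fewer than for all days. Slower values of m are shown for that reason.

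| m (days) | g = 1%, day 14 to 70 | g = 3% | g = 5% |
| --- | --- | --- | --- |
| 34.6 (all pair loss) | 0.457 to 0.484 | 0.471 to 0.555 | 0.485 to 0.629 |
| 54 | 0.456 to 0.467 | 0.468 to 0.501 | 0.481 to 0.537 |
| 60 | 0.456 to 0.465 | 0.468 to 0.495 | 0.480 to 0.526 |
| 100 | 0.455 to 0.459 | 0.466 to 0.478 | 0.477 to 0.498 |

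Worked case (g = 3%, m = 34.6, day 70): S = exp(-70/34.6) = 0.132; g_t = 0.03 / (0.03 + 0.97 x 0.132) = 0.190; RR = 0.45 / 0.810 = 0.555.

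**Recipients who leave.** With r_t the absent share of recipients, observed RR(t) = true RR x (1 - r_t) / (1 - g_t). Assume nobody is absent at matching, 0.1% per week leave in each arm, present controls are vaccinated at a rate of 0.10 per week, and present recipients have second doses from week 8 at a rate of 0.3 or 0.6 per week. At week 12, g_t = 2.28% and r_t = 3.34% or 9.62%:

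- 0.45 x 0.9666 / 0.9772 = 0.445
- 0.45 x 0.9038 / 0.9772 = 0.416

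The RR falls, which is the opposite of waning.

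**Both together.** With 2% of controls absent at matching and 0.1% per week leaving each arm, the week-12 RR runs from 0.429 (controls vaccinated at 0.05 per week, second doses at 0.6 per week) to 0.568 (controls vaccinated at 0.20 per week, no second-dose censoring).

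**With exits applied.** If absent people are neither matched nor followed, g_t and r_t are zero and the RR stays at 0.45 throughout.

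**The case against.** A reader might infer that absent registrants are visibly over-represented among controls and that the study will therefore report false waning. The population table in 5.6.1 seems to support this. Deprivation is unknown for 1.4% of the unvaccinated against 0.5% of the vaccinated (24,480/1,750,310 against 13,158/2,630,248), and smoking is unknown for 38.4% against 20.1%. The documents do not carry that inference. Those contrasts precede matching, and the unvaccinated there have a mean age of 36 against 56-59. In the matched table the markers balance: deprivation unknown 11,923 in each arm, smoking unknown 519,876 against 519,881, and households of 101+ people 231 against 150 out of 2.57 million. Balance does not show that no absent registrants remain, but it removes the documentary evidence for an excess among matched controls.

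Three further objections have force. The absent share is wholly assumed, and at 1-2% with slow control vaccination the drift is negligible. Departing recipients can offset or reverse the trend. The pre-vaccination falsification analysis in 5.5.7 might show controls already absent as a depressed event rate; however, it is only to be considered, and it would not show an absent share that builds up after matching.

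It could also be said that exits belong in the protocol. That does not dispose of the point, because 5.5.2 itself sets out the events that end follow-up, and an analyst applying it would keep leavers at risk.

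**Conclusion.** The omission is real and lies in the text: as written, the follow-up rule counts people who have left as event-free person-time in either arm, and nothing requires a control to be a current resident. The resulting error can vary with time since dose.

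Its size and net direction are not established. Considering absent controls alone, with 1-5% absent at matching and a constant true RR of 0.45, the day-70 RR lies between about 0.46 and about 0.6. The top of that range treats all pair loss as control vaccination and so overstates the drift. Whether 0.5 is crossed depends on the assumed absent share, the assumed attrition and a true RR placed just under that level. Departing recipients act the other way. The supportable conclusion is that the weekly RRs may be biased, upward if inactive registrants are common among controls, and that the plan should close the gap before analysis. It does not follow that any waning found would be false.

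**What to change.** 1. In 5.5.2, add deregistration or transfer out of the nation, by either member, as an end of follow-up for the pair. In 5.5.3, end the individual's time at risk at the same event. Use the registers each nation already holds (for example GP registration, CHI, NHAIS, WDSD).
2. In 3.5 and 5.5.2, require current registration on the match date for both recipient and control.
3. In 5.5.6, add a sensitivity analysis that repeats the weekly RRs requiring evidence of healthcare activity in a fixed period before the match date, equally of recipients and controls, where data allow. Availability differs: 3.4 lists Northern Ireland primary care data as NA, and Table 1 has no prescription item.

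The activity rule should not be imposed on controls alone. That would give the arms different eligibility, contrary to the target-trial design, and would select sicker controls.

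The cost is SAP wording, some extra linkage and coding, and slightly fewer pairs. The activity-restricted analysis drops healthy people with little healthcare contact, which is why it should stay a sensitivity analysis.

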# 1. Introduction

The aim of this study is to determine whether protection from COVID-19 vaccination wanes after the first SARS-CoV-2 vaccine dose. At present, the vaccination programme in the UK uses two dose regimens of the Pfizer-BioNTech (BNT162b2) and the Oxford-AstraZeneca (ChAdOx1) vaccines. Whilst Moderna vaccine is now available in the UK, we will not include it in this analysis due to later start date and lack of follow-up data coverage. We theorise the vaccination programme as a natural experiment which has impacts that directly arise from the vaccination itself, as well as behavioural and other responses that occur as a consequence of broader programmatic effects - for example, being asked not to attend for vaccination if symptomatic and being reminded about protective behaviours to avoid infection.

We will use pseudonymised individual level linked routinely collected primary, laboratory and vaccination healthcare data across the UK nations. All data and analyses will be hosted within a trusted research environment within each nation. Pooled estimates will be calculated across the UK nations.

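### Ending each pair's follow-up on the control's vaccination date (and on the recipient's second dose) is informative censoring when symptomatic people defer; it overstates effectiveness and can distort the waning curve

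*SAP*

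**What the plan says.** **Censoring.** In SAP section 5.5.2 a control who is vaccinated may re-enter as exposed, "after follow up is censored for the exposed-unexposed pair at the date of vaccination of the control". No lag is given. The same paragraph also ends follow-up for both members of the pair when the recipient has a second dose.

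**Deferral.** Section 1 lists, as a feature of the programme, people "being asked not to attend for vaccination if symptomatic". Section 5.5.2 repeats it ("being instructed not to attend vaccination if symptomatic") as a reason to expect effects in the first 14 days that are not due to the vaccine. It draws one consequence: "Follow up will therefore start from day 14 after the date of first dose vaccination".

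**Outcome and matching.** Section 5.2 counts an admission with a "RT-PCR confirmed positive test for SARS-CoV-2 in the 28 days prior to admission", so up to four weeks may separate the test from the event. The matching model in section 5.5.2 includes a "previous positive test indicator (tested positive previous to monthly time-period"). That indicator is fixed before each month and is not used to model censoring.

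**Sensitivity analyses.** Section 5.5.6 covers the start of the exposed period, primary-diagnosis admissions and a doubly robust estimator. Section 5.5.7 considers negative-control time periods. Neither varies the censoring rules.

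**The concern.** Censoring is harmless if, given the matching, people who leave have the same outlook as those who stay. Here they do not. A control who develops COVID-19 symptoms puts off vaccination and stays under observation until admission. A control who stays well attends, is vaccinated and removes the pair. The remaining controls are enriched for imminent events, which lowers the RR.

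The day-14 start handles deferral around the recipient's own first dose. It does not reach the control, who can be vaccinated or defer on any later day. The secondary cohort analysis in section 5.5.3 is no independent check, because unvaccinated time there also ends at vaccination.

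The second-dose rule has the same flaw on the other side. Symptomatic recipients defer, well recipients leave, and the exposed group's late event rate rises.

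The aim is to see whether effectiveness changes with time since the first dose. Both waning assessments in section 5.5.2 rely on the shape or level of estimates over that time. A bias that varies with vaccination speed and with the arrival of second doses can imitate waning or conceal it.

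**Working it through.** The plan gives no figure for this bias, so there is none to reproduce. It also gives neither the vaccination rates nor the delays, so the inputs below are assumptions unless a section is named.

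**Inputs**
- v: daily vaccination rate among controls, 1–5% (assumed).
- d: days between the start of deferral and admission. Infection to admission is taken as 10 days (assumed). If deferral starts at infection, d = 10. If it starts at symptoms on day 5 (assumed), d = 5. The SAP says symptomatic, so d = 5 is closer to its wording.
- w: daily second-dose rate among recipients (assumed).
- No true vaccine effect (RR = 1) and full compliance with deferral, unless stated.
- Threshold RR of 0.5 (section 5.5.2).

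**Step 1. Control side.** A control bound for admission escapes d days of vaccination risk, so the control event rate is inflated by about exp(v·d) and

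observed RR ≈ true RR × exp(−v·d).

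In a daily-step simulation both end days count, which gives about (1−v)^(d+1), slightly lower.

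| v per day | d = 5: exp(−vd) | d = 5: simulated | d = 10: exp(−vd) | d = 10: simulated |
|---|---|---|---|---|
| 1% | 0.95 | 0.94 | 0.90 | 0.89 |
| 2% | 0.90 | 0.89 | 0.82 | 0.80 |
| 3% | 0.86 | 0.84 | 0.74 | 0.73 |
| 5% | 0.78 | 0.74 | 0.61 | 0.57 |

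If only 70% defer, the control rate is multiplied by 0.7·exp(v·d) + 0.3. For d = 5 the RRs are then 0.97, 0.93, 0.90 and 0.83.

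**Step 2. Trend over follow-up.**
- Constant v: the same factor applies in every week, so the level is biased but there is no trend.
- Falling v, for example from 4% to 1% per day at day 42: with d = 10 the null RR goes from exp(−0.40) = 0.67 to exp(−0.10) = 0.90. With d = 5 it goes from exp(−0.20) = 0.82 to exp(−0.05) = 0.95. Either looks like waning.
- Rising v, for example from 0.5% to 4% over 70 days, with a true constant RR of 0.5 and 7 days from symptoms to event: the weekly RR falls from 0.475 to about 0.38, which would hide waning.

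**Step 3. Second-dose side.** By the same argument the recipient event rate is inflated by up to exp(w·d). With w = 4% per day from day 56 and the control side already lagged by 14 days, the null RR over days 56–76 is about 1.31–1.34 for d = 10 and 1.18 for d = 5. These are below exp(0.40) = 1.49 and exp(0.20) = 1.22 because the effect builds up after day 56.

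**Step 4. What a lag does.** A lag of m days leaves only max(d − m, 0) days of bias.
- Control lag 14, d = 10: nothing is left.
- Control lag 14, deferral from infection and 20 days to the event: 6 days are left, and at v = 4% the RR is exp(−0.24) = 0.79.
- Second-dose lag 7, d = 10: 3 days are left, at most exp(0.12) = 1.13 for w = 4%.

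**Step 5. Threshold.** A true RR of 0.60 with v = 2% appears as 0.60 × 0.82 = 0.49 (d = 10) or 0.60 × 0.90 = 0.54 (d = 5). The day-14+ counts in the section 5.6.2 template give 541/1029 = 0.53 overall, 238/488 = 0.49 for BNT162b2 and 303/541 = 0.56 for ChAdOx1, so estimates near 0.5 are realistic.

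**The case against.** The strongest reply is that the size is unknown and easily overstated. This stands. People cannot defer for symptoms they do not yet have, and starting deferral at symptoms roughly halves the bias; incomplete compliance reduces it further.

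Second, a reader might infer that the plan will produce false waning. The documents do not support that. The control-side trend needs a vaccination rate that falls with time since matching, and the SAP gives no such rate.

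Third, the quadratic test refers to the exposed group. If it concerns that group's own curve, deferral by controls does not reach it and affects only the RR curve and the 0.5 threshold. This also stands, but second-dose censoring acts on the exposed group and would reach it.

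Fourth, a reader might take the section 5.6.2 template as evidence of the bias. By subtraction, days 0–13 give 464 against 1144 events, a ratio of 0.41. That fits deferral but cannot separate the recipient's deferral from the control's, and the plan already excludes this period. Nor can a control vaccination rate be derived from the table. Its implied person-years are 2173/8.9 × 1000 ≈ 244,157 overall and 1029/4.4 × 1000 ≈ 233,864 from day 14. The difference of about 10,300 over 2,573,874 pairs is some 1.5 days per pair for days 0–13, too little for the table's implied mean follow-up of 34.6 days.

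Finally, lagging treats recently vaccinated controls as unvaccinated, although the plan expects behaviour to change after vaccination. That is a real cost.

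**Conclusion.** The concern holds as a matter of design. Given the SAP's own statement that symptomatic people stay away, censoring at the control's vaccination is informative and overstates effectiveness whenever controls are being vaccinated. Censoring at the recipient's second dose pushes late RRs upward. Nothing in the day-14 start, the matching variables or sections 5.5.6 and 5.5.7 addresses either.

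The direction of each effect follows from the text; the size does not. For 1–5% of controls vaccinated per day and an assumed 10 days from infection to admission, a null RR becomes about 0.94–0.74 (deferral from symptoms) or 0.89–0.57 (deferral from infection), both with full compliance. An upward drift without waning is possible if control vaccination slows or second doses begin during follow-up, but the documents do not show that it will occur.

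It would also be too strong to say that a 14-day lag cures the problem. Section 5.2 allows 28 days from test to admission, so events arriving later than the lag still carry bias.

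**What to change.** Add to section 5.5.6 a pre-specified matched sensitivity analysis that lags both censoring dates:
- end the pair 14 days after the control's first dose, using the plan's own 14-day window;
- for the recipient's second dose, end the pair after a lag such as the plan's own 7-day window;
- repeat with a longer lag, for example 21–28 days, in view of the 28 days in section 5.2.

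Apply the spline RR curve, the quadratic test and the 0.5 threshold to each version and report them beside the primary analysis. Also report control vaccination and second-dose rates by week since matching, so that readers can see whether the conditions for drift are present. State in advance that conclusions about waning are treated as uncertain if the analyses differ.

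The cost is two changed dates in the matched-cohort code and a few extra sets of results; no new data are needed. The lag reduces the bias without removing it, and it slightly dilutes the contrast if protection or behaviour change begins within the lag.
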